## **5. STUDY POPULATION**

### **5.1. Number of Subjects**

Sixteen subjects will be randomised to take part in Part A of the study. From these sixteen subjects, ten subjects who show the most optimal treatment effect compared to placebo on the selected dose will be asked to participate in Part B. If for any reason these subjects are unable to participate in Part B, other subjects from Part A with sufficient treatment effect will be asked to participate to ensure 10 subjects in Part B. Additional subjects may be enrolled into Part B to ensure 10 completers in Part B. If subjects prematurely discontinue the study, additional subjects may be enrolled as replacement subjects and assigned to the same treatment sequence at the discretion of the sponsor in consultation with the investigator.

### **5.2. Eligibility Criteria**

#### **5.2.1. Inclusion Criteria**

A subject will be eligible for inclusion in this study only if all of the following criteria apply:

1. Healthy Caucasian volunteers aged between 18 and 65 years of age inclusive, at time of signing the informed consent. Healthy subjects are defined as individuals who are not taking any regular medication and are free from clinically significant illness or disease as determined by their medical history (including family history), physical examination, 12-lead ECG, laboratory studies, and other tests specified in this protocol.
2. Subject has the ability to read, comprehend, and record information required by protocol, and is willing and able to provide signed and dated written informed consent prior to study participation, including compliance with the requirements and restrictions listed in the consent form.
3. Non smoker who has not smoked or used nicotine containing products for a minimum period of 6 months prior to the screening visit.
4. Subject must score greater than 40 on a COVAS scale of 0-100 for itch induced by both cowhage and histamine at screening and show a flare response with capsaicin measured by LDI scan.
5. Is willing to avoid UV exposure. i.e. use of Sun beds and sunbathing for 7 days prior to screening, throughout the study and until a week after the last dose. Subjects who require treatment with photosensitizing drugs (e.g, tetracycline, thiazides, fluoroquinolones, phenothiazines, or sulfaonamides) will be withdrawn. Subjects must also be willing to use sunscreen of SPF30 or above on the volar surface of the forearms for a week after the last dose.

6. A female subject is eligible to participate if she is of:
- Non-childbearing potential defined as pre-menopausal females with a documented tubal ligation or hysterectomy; or postmenopausal defined as 12 months of spontaneous amenorrhea [in questionable cases a blood sample with simultaneous follicle stimulating hormone (FSH) > 40 MIU/ml and estradiol < 40 pg/ml (<147 pmol/L) is confirmatory]. Females on hormone replacement therapy (HRT) and whose menopausal status is in doubt will be required to use one of the contraception methods in Section 8.1 if they wish to continue their HRT during the study. Otherwise, they must discontinue HRT to allow confirmation of post-menopausal status prior to study enrollment. For most forms of HRT, at least 2-4 weeks will elapse between the cessation of therapy and the blood draw; this interval depends on the type and dosage of HRT. Following confirmation of their post-menopausal status, they can resume use of HRT during the study without use of a contraceptive method.]
  - Child-bearing potential and agrees to use one of the contraception methods listed in Section 8.1. Female subjects willing to participate in the study must agree to use contraception from the screening visit until 15 days post-last treatment administration.
7. Male subjects must agree to use one of the contraception methods listed in Section 8.1. For male subjects willing to participate in the study this criterion must be followed from the time of the screening visit until 15 days post-last treatment
8. BMI within the range 19.0 – 32.0 kg/m^2 (inclusive).
9. AST and ALT < 2xULN; alkaline phosphatase and bilirubin ≤ 1.5xULN (isolated bilirubin >1.5xULN is acceptable if bilirubin is fractionated and direct bilirubin).
10. QTcB or QTcF < 450 msec. Note that if the initial QTc value is prolonged, the ECG should be repeated two more times (with 5 minutes between ECG readings) and the average of the three QTc values used to determine eligibility.

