## 4.5. Time and Events Table

### 4.5.1. Part A

| Procedure                                             | Screening
(up to 30 days
prior to Day
1)- May be
split over 2
days | Study Day (per treatment arm) |                |                |                |         | Follow-up

(10-14 days
post-last
dose) |
|-------------------------------------------------------|-----------------------------------------------------------------------------------|-------------------------------|----------------|----------------|----------------|---------|----------------------------------------------------|
|                                                       |                                                                                   | -30 min                       | Day 1 and 2    |                |                |         |                                                    |
|                                                       |                                                                                   |                               | 0              | 60 min         | 95 min         | 120 min |                                                    |
| Admission to Unit                                     | X                                                                                 | X                             |                |                |                |         |                                                    |
| Informed Consent                                      | X                                                                                 |                               |                |                |                |         |                                                    |
| Full Physical Exam                                    | X                                                                                 |                               |                |                |                |         |                                                    |
| Brief Physical Exam                                   |                                                                                   |                               |                |                |                |         | X                                                  |

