### 8.1.2. Male Subjects

Male subjects with female partners of child-bearing potential must use one of the following contraceptive methods after the first dose of study treatment and until the end of the follow-up visit. :

- Condom plus partner use of a highly effective contraceptive such as occlusive cap (diaphragm or cervical/vault cap) plus spermicidal agent (foam/gel/film/cream/suppository), oral contraceptive, injectable progesterone, implant of etonogestrel or levonorgestrel, estrogenic vaginal ring, percutaneous contraceptive patches, or intrauterine device. **OR**
- Abstinence, defined as sexual inactivity consistent with the preferred and usual lifestyle of the subject. Periodic abstinence (e.g. calendar, ovulation, symptothermal, post-ovulation methods) and withdrawal are not acceptable methods of contraception

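### Section 8.1.2 ends the male contraception requirement at the follow-up visit, 1 to 5 days before the 15 days set by inclusion criterion 7

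*Protocol*

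**What the plan says.** The Protocol states a contraception period for men in two places.

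- **Section 5.2.1, inclusion criterion 7.** "Male subjects must agree to use one of the contraception methods listed in Section 8.1", and "this criterion must be followed from the time of the screening visit until 15 days post-last treatment".
- **Section 8.1.2, Male Subjects.** Men with female partners of child-bearing potential must use one of the listed "contraceptive methods after the first dose of study treatment and until the end of the follow-up visit".

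The follow-up visit is dated in the Time and Events Tables. The Part A table (4.5.1) puts it at "10-14 days post-last dose", and the Part B table (4.5.3) gives the same window.

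For women, inclusion criterion 6 says those of child-bearing potential "must agree to use contraception from the screening visit until 15 days post-last treatment administration". Section 8.1.1 lists their methods and gives no start or end date.

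**The concern.** The two male rules are both current text, both mandatory and both about the same precaution, but they end on different days. Criterion 7 counts days from the last treatment. Section 8.1.2 ties the end to a visit whose whole window closes before day 15. Criterion 7 also points the reader to Section 8.1, so the place where staff look up what men must do is the place that carries the shorter period.

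At stake is when men with partners of child-bearing potential are told the precaution ends. Staff working from 8.1.2 could release them at the follow-up visit, and the man would then depart from criterion 7 without knowing it. The Part A table records discharge at that visit and schedules nothing after it, so no later planned contact would put this right.

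**Working it through.** No figure in the Protocol needs reproducing here. The check is date arithmetic on stated periods.

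**Inputs**

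- End of male contraception under criterion 7 (Section 5.2.1): day 15 after the last treatment.
- End of male contraception under Section 8.1.2: the end of the follow-up visit.
- Follow-up visit window (Sections 4.5.1 and 4.5.3): day 10 to day 14 after the last dose, in both parts.

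**End date**

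Shortfall = 15 − (day of follow-up visit).

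| Follow-up visit, days after last dose | Shortfall against criterion 7 |
|---|---|
| 10 | 15 − 10 = 5 days |
| 11 | 15 − 11 = 4 days |
| 12 | 15 − 12 = 3 days |
| 13 | 15 − 13 = 2 days |
| 14 | 15 − 14 = 1 day |

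The shortfall is at least 1 day and at most 5, and 0 of the 5 permitted visit days gives no shortfall. Scheduling within the window therefore cannot reconcile the two rules. Only a visit held late, outside the window, would.

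**Start date**

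Criterion 7 starts at screening and 8.1.2 starts after the first dose. No study drug is given between the two, so this difference is a compliance mismatch and has no bearing on exposure.

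**Which text is out of line**

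Three contraception periods are stated: criterion 6 (women), criterion 7 (men) and 8.1.2 (men). The first two run from screening to 15 days after the last treatment, and only 8.1.2 differs. Its window lies wholly inside that of criterion 7, so a man who follows criterion 7 meets both rules, while a man who follows 8.1.2 exactly meets only one.

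**After the change**

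If 8.1.2 takes the period in criterion 7, the shortfall is 15 − 15 = 0 days whatever the visit day.

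**The case against.** The best reply is that nothing here forces a wrong action. Section 8.1.2 says what men must do up to follow-up. It does not say that they may stop then or that criterion 7 lapses. Because the periods are nested, the stricter rule still binds and no one faces incompatible duties. That is correct, and it is why the point is minor. But the Protocol does not say which section prevails, and 8.1.2 states its own end point without referring back to criterion 7.

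A second reply is that 8.1.2 may be the intended rule. Section 7.4.1 collects pregnancies, including those in partners of male subjects, from the start of dosing to the end of follow-up, and Section 13 collects adverse events until the follow-up contact. On that view criterion 7 could be shortened instead, and extending 8.1.2 would carry contraception past the end of pregnancy collection. Those sections govern reporting, however, not contraception. Criteria 6 and 7 already run past the collection period for both sexes, so aligning 8.1.2 creates no new gap. The documents do not prove which end date was meant. The longer one is the safer choice because it satisfies both rules as written.

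A third reply is that no harm is shown. This also stands. The Protocol gives no washout argument for day 15, expects less than 10% of the applied drug to be measured in plasma (Section 1.7.1), and caps the total dose at 95 mg across both parts (Section 4.4). The case is for one clear rule and does not claim that the missing days are dangerous.

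**Conclusion.** The inconsistency is real. Section 8.1.2 ends the male precaution 1 to 5 days before criterion 7 does, at every on-schedule follow-up visit in both parts. It matters only for men with female partners of child-bearing potential who are guided by 8.1.2, and it assumes that the follow-up visit falls within its stated window.

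The point is minor. It concerns consistency of conduct and a reproductive-safety precaution, and it does not change eligibility at entry, any endpoint, the sample size or the analysis. It is worth correcting because the section that lists the methods gives the shorter period and the correction costs almost nothing.

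**What to change.** In Section 8.1.2, replace the stated period with the one in criterion 7, so that men with female partners of child-bearing potential use a listed method from the screening visit until 15 days after the last treatment administration. This also removes the start-date mismatch and matches the period already set for women in criterion 6.

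Optionally, name the same population in criterion 7, which now reads as covering all male subjects. The main repair does not depend on this.

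The cost is one line in 8.1.2 and, if wanted, a few words in criterion 7. No visit, test or subject is added. At the follow-up visit, men would need to be told that the precaution continues to day 15.

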### 5.2.2. Exclusion Criteria

Deviations from exclusion criteria are not allowed because they can potentially jeopardise the scientific integrity of the study, regulatory acceptability or subject safety. Therefore, adherence to the criteria as specified in the protocol is essential.

A subject will not be eligible for inclusion in this study if any of the following criteria apply:

1. Suffers from skin infection or inflammation of the forearm, or has other arm skin irregularities that may in the opinion of the investigator interfere with study assessments (e.g. nevi, tattoos).
2. The subject suffers from eczema, psoriasis or any other acute or chronic dermatological problem if, in the opinion of the investigator this is likely to interfere with study assessments

3. Any subject with localised sunburn in the area to be treated as part of the study.
4. History of regular alcohol/drug consumption within 6 months of the study. Regular alcohol consumption defined as: an average weekly intake of >21 units for males and >14 units for females. One unit is equivalent to 8 g of alcohol: a half-pint (~240 ml) of beer, one glass (125 ml) of wine or one (25 ml) measure of spirits.
5. A positive pre-study drug/alcohol screen at screening visit. A minimum list of drugs that will be screened for include amphetamines, barbiturates, cocaine, opiates, cannabinoids and benzodiazepines.
6. The subject has participated in a clinical trial resulting in exposure to more than four new chemical entities within 12 months prior to the first dosing day or has received an investigational product within the following time period prior to the first dosing day in the current study: 90 days, 5 half-lives or twice the duration of the biological effect of the investigational product (whichever is longer).
7. Unable to refrain from use of prescription or non-prescription drugs. Refer to Section 9 for details.
8. History of sensitivity to any of the study medications SB705498, challenge agents or components thereof or a history of drug or other allergy that, in the opinion of the investigator or GSK Medical Monitor, contraindicates their participation.
9. Where participation in the study would result in donation of blood or blood products in excess of 500 mL within a 56 day period following completion of the study.
10. Lactating females.
11. A positive pre-study Hepatitis B surface antigen or positive Hepatitis C antibody result within 3 months of screening
12. A positive test for HIV antibody.
13. Excessive caffeine drinkers (~5 or more cups a day) or the subject is unable to commit to refraining from caffeine-containing products for 24hrs prior to each assessment visit and whilst present in the unit.

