| Medical/medication/
drug/alcohol history           | X                                                                                 |                               |                |                |                |         |                                                    |
| Vital signs                                           | X                                                                                 | X                             |                |                |                |         | X                                                  |
| ECG                                                   | X                                                                                 | X                             |                |                |                |         | X                                                  |
| Urine Drug/Alcohol                                    | X                                                                                 | X                             |                |                |                |         |                                                    |
| Serum β-hCG (women)- Day 1 only                       | X                                                                                 | X                             |                |                |                |         | X                                                  |
| HIV, Hep B and Hep C screen-                          | X                                                                                 |                               |                |                |                |         |                                                    |
| Haem/Chem/Urinalysis tests                            | X                                                                                 |                               |                |                |                |         | X                                                  |
| Administration of SB705498 cream/Placebo  |                                                                                   |                               | X              |                |                |         |                                                    |

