2. LDI scan will be performed after application of SB705498 cream or placebo. Cream is applied, left for 1 hr and excess is then removed to allow scanning.
3. LDI scan will be performed 5 mins after the Capsaicin cream is wiped off the arm.
4. Application of the cream/placebo followed by capsaicin challenge and LDI scanning will be performed twice on each day. i.e. 4 applications over the 2 days with the 3 different doses of SB705498 and placebo.

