## **7. STUDY ASSESSMENTS AND PROCEDURES**

This section lists the parameters of each planned study assessment. The exact timing of each assessment is listed in the Time and Events Table (Section 4.4). Detailed procedures for obtaining each assessment are provided in the Study Procedures Manual (SPM). Whenever vital signs, 12-lead ECGs and blood draws are scheduled for the same nominal time, the assessments should occur in the following order: 12-lead ECG, vital signs, blood draws. The timing of the assessments should allow the blood draw to occur at the exact nominal time.

The timing and number of planned study assessments, including safety, pharmacokinetic and pharmacodynamic assessments may be altered during the course of the study based on newly available data (e.g. to obtain data closer to the time of peak plasma concentrations) to ensure appropriate monitoring. The change in timing or addition of time points for any planned study assessments must be approved and documented by GSK, but this will not constitute a protocol amendment. The IRB/IEC will be informed of any safety issues that require alteration of the safety monitoring scheme. No more than 500 mL of blood will be collected over the duration of the study, including any extra assessments that may be required.

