## **7.5. Pharmacokinetics**

### **7.5.1. Blood Sample Collection**

Blood samples for pharmacokinetic analysis of SB705498 will be collected at the time points indicated in Section 4.4, Time and Events Table. The actual date and time of each blood sample collection will be recorded.

Details of PK blood sample collection (including volume to be collected), processing, storage and shipping procedures are provided in the Study Procedures Manual (SPM).

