## **10. COMPLETION OR EARLY WITHDRAWAL OF SUBJECTS**

### **10.1. Subject Completion**

A completed subject is one who has completed all phases of the study including the follow-up visit.

The end of the study is defined as the last subject's last visit.

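### Exclusion criterion 9 counts study blood only after the last scheduled draw, so as worded it cannot exclude anyone at screening

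*Protocol*

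**What the plan says.** Protocol Section 5.2.2, criterion 9, sets two conditions. The blood must be given because of the trial ("Where participation in the study would result in donation of blood"), and the amount must be "donation of blood or blood products in excess of 500 mL within a 56 day period following completion of the study". The preamble to the same section allows no deviations and asks sites to apply the criteria as specified.

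Section 10.1 defines completion: "A completed subject is one who has completed all phases of the study including the follow-up visit". It adds: "The end of the study is defined as the last subject's last visit".

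Section 7 sets a separate ceiling: "No more than 500 mL of blood will be collected over the duration of the study, including any extra assessments that may be required".

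Sections 4.5.1 to 4.5.3 give the sampling times. Section 7.5.1 leaves the PK sample volume to the Study Procedures Manual.

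**The concern.** A volunteer-safety exclusion should be able to exclude someone. This one starts counting when the study has stopped taking blood, and it counts only blood that the study causes to be given. If both conditions are read as written, no one can meet them at screening.

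The person such a limit would be expected to catch is someone who gave blood shortly before screening and would then add the study draws. That person passes criterion 9, and no other criterion asks about blood donation. Because deviations are not allowed, a site that reads in the probable intent applies a rule that is not on the page, while a site that follows the text excludes nobody. Neither monitoring nor consistent application is possible.

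**Working it through.** The protocol states no figure to reproduce. The check sets the draw schedule against the definition of completion, then sizes the consequence.

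**1. When scheduled blood is taken**

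| Draw | Timing | Source |
|---|---|---|
| "Haem/Chem/Urinalysis tests" | Screening and follow-up | 4.5.1, 4.5.3 |
| HIV and hepatitis screen | Screening | 4.5.1, 4.5.3 |
| Serum hCG (women) | Screening, dosing, follow-up | 4.5.1, 4.5.3 |
| PK samples | Part A, Days 1 and 2 | 4.5.1, 4.5.2 |

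The PK count follows from four samples per application and "i.e. 4 applications over the 2 days with the 3 different doses of SB705498 and placebo": 4 × 4 = 16.

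Neither table has a column after follow-up, which is 10–14 days after the last dose. Under Section 14, liver follow-up sampling comes before the subject is withdrawn from the study, so it is not scheduled post-completion blood either.

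**2. Blood in the window that the criterion names**

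Completion covers all phases including follow-up. A subject who enters Part B therefore completes only after Part B. Scheduled study blood in the following 56 days is 0 mL, against a threshold of more than 500 mL. Taking the last subject's last visit as the reference point only moves the window later.

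**3. Would moving the window be enough?**

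No. With study blood capped at 500 mL by Section 7, participation alone cannot give more than 500 mL in any window. The criterion can have an effect only if blood given outside the study is counted too.

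**4. Does the study fit within 56 days?**

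- Part A alone: at most about 30 + 2 + 14 = 46 days, under 56.
- Part A and then Part B without rescreening, which Section 4.5.3 allows up to 60 days from Part A screening to the first Part B visit: about 60 + 2 + 14 = 76 days, over 56. With rescreening it is longer.

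A single fixed 56-day window therefore cannot cover every subject.

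**5. Size of the consequence**

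The protocol gives no sample or donation volumes, so all per-draw volumes below are assumptions.

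- PK: 16 × 2–10 mL = 32–160 mL
- Haematology and chemistry: 2 × 5–15 mL = 10–30 mL
- Virology: 1 × 5–10 mL = 5–10 mL
- Serum hCG: 3 × 0–5 mL = 0–15 mL

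Part A total: 32 + 10 + 5 + 0 = 47 mL to 160 + 30 + 10 + 15 = 215 mL.

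With an assumed outside donation of 450–500 mL in the same 56 days: 47 + 450 = 497 mL to 215 + 500 = 715 mL. The upper end is 715/500 = 1.43 times the criterion's own limit. Part B draws are not in this sum.

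**The case against.** Several points on the other side are fair.

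- **Other protection exists.** A reader might infer that volunteers have no working safeguard against blood loss. The protocol does not support that. The Section 7 cap limits what the study itself takes. Screening haematology includes haemoglobin and hematocrit (Section 7.2), and inclusion 1 requires health judged partly on laboratory results. Exclusion 6 keeps out anyone given an investigational product within at least 90 days, which removes much blood loss from recent trials. The investigator may withdraw a subject for safety (Section 10.2). This stands, although no haemoglobin threshold for eligibility is given and none of these rules asks about an ordinary blood donation.
- **A large total loss is not shown.** A reader might add a 450–500 mL donation to the full cap and arrive at 950–1000 mL, about twice the limit. That treats the ceiling as the planned volume. The documents do not say the study takes 500 mL, and the assumed draws come to well under half of it.
- **A kinder reading exists.** The wording may be meant to stop volunteers donating soon after the study. The reference to the time after completion makes that plausible, but a later voluntary donation is not something participation results in, and Section 8 contains no such restriction. Even so read, it would miss a donation made before screening.
- **Later draws are possible.** Section 13.6 follows adverse events to resolution and allows extra tests. This is why the statement is limited to scheduled blood. Such draws cannot be foreseen at screening, so they cannot serve as an eligibility test.
- **Counting earlier donations is an addition.** The protocol does not now claim to count them, so this part of the remedy goes beyond correcting the window. That is right, but without it the criterion would still have no effect.

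**Conclusion.** The criterion does not work as worded. Its window begins after the last scheduled draw, and the Section 7 cap independently prevents its threshold from being reached through participation. That conclusion needs no assumed volumes. It rests on the plain text of Sections 5.2.2, 7 and 10.1 and on the Time and Events tables.

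The practical effect is limited to volunteers who gave or lost blood elsewhere close to the study. For them the illustrative total runs from just under the limit to about 1.4 times it. This range depends wholly on assumed sample and donation volumes and would change once the Study Procedures Manual volumes are known. Endpoints, randomisation and analysis are not affected. Severity is minor.

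**What to change.** Reword criterion 9 and reconcile it with the Section 7 cap:

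- Remove the phrase tying the 56 days to study completion.
- Apply the protocol's own 500 mL limit to planned study blood plus blood donated or lost outside the study.
- Make the 56 days a rolling period: any 56-day period that overlaps screening through follow-up of Part A and, where applicable, Part B.
- If a restriction on donating after the study is also intended, state it separately in Section 8 as a restriction on subjects and not as an eligibility test.

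The cost is a short protocol amendment, one question at screening, and the deferral of a few recent donors. The 500 mL and 56-day figures stay as they are.
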